### Interventions

The intervention group will download a stress-managing app, the app can be used on mobile devices including mobile phones and tablets etc. The app will be based on Stress Inoculation Training (SIT) developed by Meichenbaum (29). Even though SIT was designed for military settings, there has been a lot of studies which adapted the SIT and use it among students and adolescents (30-34) and delivered SIT via technologies (35). Our study will modify SIT to high school context by adding assertiveness and training participants cognitive and behavioural techniques to deal with stressors arising from academic environment and peer interpersonal relationships. The online stress-managing intervention will comprise of 11 sessions which consist of psychoeducation, problem assessments, training of stress coping skills (emotion-focused coping skills and problem-focused coping skills), cognitive restructuring, imagery and behavioural rehearsal and role play (see [Appendix 1](#_Appendix_1) for details of the intervention content). The intervention content will be in Chinese language. The control group will not be given access to the app until the termination of the trial (12 weeks after the start of the trial). There will be no other intervention given to the control group. Both the intervention group and the control group will have full access to usual care, which is the psychological courses arranged by the high schools.

The criteria for discontinuing for a given trial participant include: (i) if they self-reported or reported by others to be suicidal; (ii) if they drop out of school during the intervention period; (iii) if they require to withdraw from the study.

Strategies to improve adherence to intervention protocol include:

- Instructions about the importance of following study guidelines for adherence to once weekly product.
- Instructions about the purpose and use of the intervention app.
- Notification sent via app weekly on each Sunday that there will be a session taken in the app.
- Successfully completion of each session will generate a virtual star in the participant’s account as a reward for the participation.
- Adherence assessments include log in times and other usage data collected in the app.

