### Harms

In our study an adverse event will be defined as serious psychological distress experienced by participants without regard to the possibility of a causal relationship. Adverse events will be collected after the subject has provided consent and enrolled in the study. If a subject experiences an adverse event after the informed consent document is signed but the subject has not started to receive study intervention, the event will be reported as not related to study intervention. All adverse events occurring after entry into the study will be recorded. If an adverse event meets the criteria for a serious adverse event after study enrolment, this will be reported to Centre for Online Health, The University of Queensland. If the participant drop out as a result of an adverse event, study personnel will document the circumstances and data leading to discontinuation of the intervention. A serious adverse event for this study is any occurrence that is believed by the investigators to be causally related to the intervention and results in any of the following: Life-threatening condition (i.e., suicidal ideation or attempts), hospitalization due to mental health conditions, drop out of school.

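### A serious adverse event must be judged to be caused by the app, so until at least week 12 control-arm outcomes cannot be classed or escalated as serious, and serious-event counts cannot be compared between arms

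*Protocol*

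**What the plan says.** All the rules are in the protocol, mostly under Harms.

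- **Adverse event.** It is "serious psychological distress experienced by participants without regard to the possibility of a causal relationship". All such events after study entry are recorded, in either arm.
- **Serious adverse event.** The definition has two conditions. The first is causal: "A serious adverse event for this study is any occurrence that is believed by the investigators to be causally related to the intervention". The second is an outcome from this list: "Life-threatening condition (i.e., suicidal ideation or attempts), hospitalization due to mental health conditions, drop out of school".
- **Onward reporting.** An adverse event that meets the serious criteria is reported to the Centre for Online Health at the sponsoring university. No such step is stated for other events.
- **Events before exposure.** After consent, if the student has yet to begin the intervention, "the event will be reported as not related to study intervention".
- **Control condition.** Under Interventions: "The control group will not be given access to the app until the termination of the trial", which that section places at 12 weeks. Trial design also says 12 weeks. Allocation says 16 weeks. Outcomes are collected at baseline, 12 and 16 weeks (Data collection methods).
- **Blinding.** Neither participants nor researchers are blinded after assignment.

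**The concern.** Seriousness describes what happened to the participant. Relatedness is an opinion about why. The Harms section merges them into a single test, and the opinion is about an app that only one arm has. The same outcome is therefore handled differently according to allocation.

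Two things are at stake. One is oversight: the participants are high-school students who identify themselves as stressed, the discontinuation criteria anticipate suicidality, and the protocol plans neither interim analyses nor auditing. A serious outcome that is not escalated has no other stated route to the sponsor's centre. The other is interpretation: any table of serious events by arm would reflect the definition and the investigators' opinions as well as the students' experience. A later analysis plan cannot recover events that were never classified or reported.

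**Working it through.** The protocol states no harms figure, so there is none to reproduce. The check is to follow one outcome through the rules in each arm, then show the possible scale.

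**Step 1: the same outcome in each arm.** Take a student hospitalised for a mental health condition in week 8.

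| Question | Intervention arm | Control arm |
| --- | --- | --- |
| Has the student had the app? | Yes, if started | No, on either access date |
| Can it be judged caused by the app? | Yes, by investigators who know the arm | No; read literally, the pre-start rule also fixes the answer as not related |
| Is it classed as serious? | Only if attributed to the app | No |
| Is it reported to the sponsor's centre? | Only if classed as serious | No |
| Is it recorded as an adverse event? | If it counts as serious psychological distress | If it counts as serious psychological distress |

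The causality condition alone produces the control column, since an app that was not used cannot be believed to have caused the event. The pre-start rule only reinforces it.

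**Step 2: how long this lasts.** Under Allocation (access after 16 weeks) it covers the whole of follow-up. Under Trial design and Interventions (access after 12 weeks) it covers weeks 0 to 12; a control student who then takes up the app could have a qualifying event in weeks 12 to 16. Both readings share the period up to week 12.

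**Step 3: gap in the record.** The reporting sentence starts from an adverse event, and an adverse event is defined as distress. A hospitalisation or school drop-out that nobody records as distress has no stated route into the adverse event record, in either arm.

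**Step 4: effect on the counts.** Let p be the true proportion with a listed outcome while controls have no app, equal in both arms, and q the share of intervention-arm outcomes attributed to the app. With 150 per arm (Sample size):

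- true expected counts: 150p in each arm
- expected counts classed as serious: 150pq (intervention) against 0 (control)

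The apparent difference is 150pq, although the true difference is zero. For an assumed p = 2%, the truth is 150 × 0.02 = 3 against 3. The classified counts range from 0 against 0 (q = 0) to 3 against 0 (q = 1). The definition can therefore hide events or suggest an imbalance, depending on q.

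**Step 5: how likely the rule is to matter.** The rates are assumptions, and students are treated as independent. Expected controls affected = 150p; chance of at least one = 1 − (1 − p)^150.

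| Assumed p | Expected controls affected | Chance of at least one |
| --- | --- | --- |
| 0.5% | 0.75 | 53% |
| 1% | 1.5 | 78% |
| 2% | 3.0 | 95% |
| 5% | 7.5 | >99.9% |

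None of these outcomes could be classed as serious while the student has no app.

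**The case against.** The strongest reply is that much of the safety information survives. Adverse events are recorded in both arms whatever their cause, and suicidal ideation is plausibly serious psychological distress. If a participant drops out because of an adverse event, the circumstances are documented with no causality condition. Suicidality and school drop-out are discontinuation criteria in either arm, and a student in either arm who needs mental health assistance is referred and counted as a drop-out. This stands. A reader might infer that serious events among controls leave no trace, and the documents do not support that. What is lost is the serious classification and the onward report, plus the gap in Step 3.

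A reader might also infer that the control arm can never have a serious adverse event. That holds only if access comes at 16 weeks; on the 12-week reading such an event is possible in weeks 12 to 16.

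A third tempting reading is that the serious definition contradicts the adverse event definition, which applies "without regard to the possibility of a causal relationship". It does not. A narrower category with added conditions can sit inside a broader one. The definition is unsuitable, not inconsistent.

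The pre-start sentence was probably written for the gap between consent and first use. That is fair, and the point does not depend on it. The sentence also shows that relatedness is already assigned to some events, so recording it separately is a small step.

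Finally, the protocol plans no between-arm test of serious events and gives no rates, and it randomises by class. A significance test on hypothetical counts would therefore prove nothing. The distortion affects any comparison or tabulation of serious events by arm; the efficacy analysis is untouched.

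**Conclusion.** The serious adverse event definition is wrong as written. Until at least week 12, a control student's suicidality, mental-health hospitalisation or school drop-out cannot be classed or escalated as serious. In the intervention arm the same outcome qualifies only on an unblinded attribution to the app. Serious-event counts therefore cannot be compared between arms.

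This follows from the definitions and needs no assumed rate. The size does need one: for true proportions of 0.5% to 2%, between 0.75 and 3 of 150 controls would be expected to have an outcome that the rule excludes. Those figures assume independent students; clustering within classes would leave the expected numbers unchanged but could alter the chance of at least one. The direction of any distortion cannot be predicted, because it depends on how often investigators attribute events to the app.

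**What to change.** In the Harms section:

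1. Define a serious adverse event by the listed outcomes alone, in both arms, whatever the judged cause. Make any listed outcome recordable even if it was not first recorded as distress.
2. Record relatedness to the intervention as a separate field, and state that it affects neither classification nor reporting.
3. Report every event meeting the outcome criteria to the sponsor's centre.
4. Tabulate serious events by arm regardless of relatedness; relatedness can be shown alongside.

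Separately, the 12-week access date in Trial design and Interventions must be reconciled with the 16-week date in Allocation, so that it is clear how long controls remain without the app.

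The cost is a few sentences of protocol text and a handful more reports. Sample size, randomisation and the efficacy analysis do not change.

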### Auditing

There will not be auditing trial conduct.

# Ethics and Dissemination

### Research ethics approval

As this study will be conducted at multiple sites in two countries: Australia and China. We will therefore obtain ethics approval from Tianjin Normal University Ethics Committee in China and The University of Queensland Human Ethics Office in Australia. Participants under 18 years will give consent signed by their parents or guardians. Participants >=18 years will give consent signed by themselves. In addition, Participants will be given a Participants Information Sheet which describes the detail of the project and potential benefits and risks before giving consent to participate in this study.

### Protocol amendments

Amendments of the protocol will be discussed within research team members. Approval of amendments will also be obtained from Tianjin Normal University Ethics Committee in China and The University of Queensland Human Ethics Office in Australia.

### Consent or assent

Principal investigator (XZ) will send and collect paper consent forms from participants for assignment from their guardians, head teachers and themselves.

### Confidentiality

All information collected from this study will be treated as strictly confidential. All the data will be kept in a locked filing cabinet or on a password-protected computer in a secure office at the Centre for Online at the University of Queensland. All reporting about the research will be aggregated so that no individual can be identified. The information about the participants will be kept separately from the data. Only the research team members can access the identified data. The data used for published reports will not have any information relating to personal details of the participants.

### Declaration of interests

There is not competing interests in this study.

### Access to data

Only the research team members will have access to the final trial dataset. There is no contractual agreements that limit such access for investigators.

### Ancillary and post-trial care

Participants who suffer from psychological distress as a result of the intervention will receive free counselling from the principal investigator (XZ). The principal investigator is a registered psychological counsellor in China, XZ is also experienced with conducting individual and group psychotherapy with adolescents and school students.

### Dissemination policy

If participants are interested in the result of the study, they will send their email address to the contact person of the study ([name]). The results of this study will be published in a peer-reviewed journal. The results will be send to interested individual participants via the email address they provided. We will not use professional writers. There is no plan for granting public access to the full protocol, participant-level dataset nor statistical code.

Informed consent materials can be found in [Appendix 2](#_Appendix_2).

# Appendices

## Appendix 1

The details of the intervention content

| **First phase:**  **Conceptualization** | **Aims:**   1. Build relationship with the participants 2. Introduce the online intervention: stress inoculation training, targeted mental health conditions; outcomes the participant may expect from the intervention 3. Introduction about confidentiality and privacy 4. Implement assessments 5. Analyse current problems   **Duration:**  30 minutes  **Techniques:**   1. Interview 2. Imagery recall 3. Self-monitoring 4. Behavioural assessment 5. Psychological testing | **Session 1:**  1. Introduction about the online intervention and ethical considerations;  2. implement assessments: PSS-10; DASS-21; FS-8; CISS-SFC  3. what is stress, coping strategies, emotions; and the transactional nature of psychological stress  **Session 2:**  Analyse current problem (nature of the participant’s stress and coping strategies)  **Session 3:**  Offer a conceptual model of the participant’s stress reactions |
| --- | --- | --- |
| **Second phase:**  **Skills acquisition and rehearsal phase** | **Aims:**  1. ensure that the participant develop the capacity to effectively execute coping responses  2. collect information about the participant’s attitudes and expectations for each particular training technique that is introduced.  3. nurture a flexible coping repertoire and to work with participants collaboratively, to select, test, and assess the merits of various coping procedures  4. teach the participant coping skills  **Duration:**  30 minutes  **Approaches:**  1. clinical interview  2. attuned ear for distorted thinking styles  3. evaluate the participant logically  4. use of 0-100 scale in the appraisals of stressful situations  5. Ellis ABC approach | **Session 4: relaxation skills training**  1. introduce the stress-tension cycle.  2. tap the participant’s previous experience with, concern with, and expectations concerning relaxation.  3. teach the participant relaxation skills through guided relaxation and deep breathing.  4. encourage the participant to apply the relaxation skills into daily life.  **Session 5: coping strategies-cognitive restructuring**  1. “thought catching”—help the participant become aware of automatic thoughts.  2. introduce common “thought distortions”: generalization, “must” or “should” statements, black and white thinking, catastrophizing, jump to conclusions, emotional thinking, ignore positive, personalization, predict the future, read others’ minds.  3. help the participant recognize that their thoughts are not usually the facts, but the hypotheses worthy of testing.  4. encourage participants to do personal experiments about their thoughts.  **Session 6 and 7: problem-solving training**  1. problem identification--define stressors or stress reactions as a problem to be solved.  2. goal selection—set realistic goals as concretely as possible by stating the problem in behavioural terms and by delineating steps necessary to reach each goal.  3. generation of alternatives—generate a range of possible alternative courses of action.  4. change of position—imagine how others might respond if asked to deal with similar stress problem.  5. Evaluation—evaluate the pros and cons of each proposed solution and rank order the solutions from least to most practical and desirable.  6. strategy rehearsal—rehearse strategies and behaviours by means of imagery, behavioural rehearsal, and graduated practice.  7. encourage and reward—expect failures but reward self for having tried.  **Session 8: self-instructional training, or guided self-dialogue**  1. Review with the participant the various stages if their .stress experience (i.e., preparation for stressors, confrontation, critical moments and self-reflection)  2. work with the participant to generate adaptive self-statements for 4 stages of stress experience (i.e., preparing for stressor; confronting and handling the stressor; coping with feelings of being overwhelmed; evaluation of coping efforts and self-rewards)  **Session 9: assertiveness**  1. Help participants understand what is assertiveness and the benefits of being assertive.  2. Help participants distinguish between passive, aggressive and assertive communication  3. Train participants with assertive techniques |
| **Third phase:**  **Application and follow-through** | **Aims:**  1. To encourage the participant to implement coping responses in day-to-day situations.  2. To maximize chances of generalized change  **Approaches:**  1. imagery rehearsal  2. behavioural rehearsal  3. role play  4. modelling  5. graduated in vivo practice | **Session 10: Imagery rehearsal**  1. The app help the participant with generating a hierarchy of scenes, from least to most stressful. Usually the length lasts in 1-5 minutes  2. The participant is encouraged to use any personally generated self-statements and images that would facilitate coping.  3.If the participant experience difficulty in reducing stress for any one scene, the app can either (i) go back to a less intensely stressful scene from the hierarchy or (ii) discuss with the participant about his/her “catastrophizing” self-statement when the participant become overwhelmed  4. Throughout the imagery rehearsal procedure, always check with the participant about his/her reactions to the imagery process, discussing the participant’s ability to visualize and when they can use coping techniques in vivo.  **Session 11: behavioural rehearsal, role play and modelling**  1. The app role play with the participant to practice coping skills (communication skills, mobilizing social support, and anger control)  2. The app shows short videos of others coping with stressful events, and discuss with the participant about other people’s coping efforts.  **Session 12: Relapse prevention and follow-through**  1. The app encourage participants to anticipate failures and setbacks  2. The app work with the participant to rehearse how they will respond to such lapses  3. The app can use spontaneous relapses that occur during the course of training as opportunities to develop resilience  4. help the participant to normalize setbacks, and educate the participant that our aim is not to eliminate stress, but use the stress constructively  5. The app convey to the participant that the “door is always open”, and encourage the participant to seek additional help if needed  6. Provide the participant with additional help resources the participant can seek when needed. |
